## Abstract

**Background:**

Adherence and persistence to positive airway pressure (PAP) therapy are key factors for positive health outcomes. Home support providers participate in the home implementation and follow-up of PAP therapy for patients with obstructive sleep apnea (OSA). In Europe, home support provider service levels are country (or area) specific, resulting in differences in content and frequency of patient interactions. However, no robust evaluation of the impact of these differences on clinical and patient outcomes has been performed.

**Objective:**

The AWAIR study aims to evaluate and compare the impact of different home support provider service levels on PAP adherence and persistence in 4 European countries.

**Methods:**

This real-world, ambispective, cohort study—conducted in France, Belgium, Spain, and Portugal—will recruit adults with OSA who started PAP therapy between 2019 and 2023 and were followed by an Air Liquide Healthcare home support provider. Given the large number of eligible participants (around 150,000), the study will use a decentralized and digital approach. A patient video will present the study objectives and the participation process. A secure electronic solution will be used to manage patient information and consent, as well as to administer a web-based questionnaire. Retrospective data, collected during routine patient follow-up by home support providers, include the level of service and device data, notably PAP use. Prospective data collected using an electronic patient-reported outcome tool include health status, OSA-related factors, patient-reported outcomes including quality of life and symptoms, OSA and PAP literacy, patient-reported experience, and satisfaction with PAP therapy and service. Hierarchical models, adjusted for preidentified confounding factors, will be used to assess the net effect of home support provider services on PAP adherence and persistence while minimizing real-world study biases and considering the influence of country-level contextual factors. We hypothesize that higher levels of home support provider services will be positively associated with adherence and persistence to PAP therapy.

**Results:**

As of December 2024, the study has received approval in France, Portugal, and 2 regions of Spain. The study began enrollment in France in October 2024. Results are expected in the second quarter of 2025.

**Conclusions:**

The AWAIR study has a unique design, leveraging an unprecedented number of eligible participants, decentralized technologies, and a real-world comparative methodology across multiple countries. This approach will highlight intercountry differences in terms of patient characteristics, PAP adherence, and persistence, as well as patient-reported outcomes, patient-reported experiences, and satisfaction with the home service provider. By assessing the added value of home support provider services, the results will support best practices for patient management and for decision-making by payers and authorities.

**International Registered Report Identifier (IRRID):**

PRR1-10.2196/65840

## Introduction

Obstructive sleep apnea (OSA) is the most prevalent form of sleep-disordered breathing, affecting nearly 1 billion adults aged 30-69 years worldwide [1]. OSA is characterized by repetitive collapse of the upper airway during sleep, resulting in complete (apnea) or partial (hypopnea) airway obstruction [2]. OSA can cause daytime symptoms that impair quality of life and has been linked with a variety of cardiometabolic diseases, neurocognitive impairment, depression, road traffic accidents, and all-cause mortality [3-12]. Identification and management of OSA are therefore important to reduce those risks.

Positive airway pressure (PAP) therapy remains the gold standard treatment for severe OSA because high-quality evidence and long-term assessment are lacking for noncontinuous PAP therapies [13,14]. PAP therapy has been shown to reduce road traffic accidents, blood pressure, cardiovascular risk, and health care use [15-19]. However, the effectiveness and cost-effectiveness of PAP therapy are linked to sufficient daily device use, with regular and continued long-term usage [16,19-24], which appears challenging in all geographies [25,26].

In most European countries, home support provider companies supply the PAP device and support its use by the patient. However, the type and level of services provided differ markedly between countries. Services can range from mainly logistical support (ie, device delivery in Belgium, Germany, and the Netherlands) to a personalized support plan for patients integrating motivational interviews to enhance adherence (as in some regions of Spain and Portugal) [27-29]. Also, the number of regulated home visits varies from none to several per year (like in France and Portugal). The use of PAP telemonitoring also varies widely, being routine for almost all patients in France throughout the PAP treatment period [30] but not used (or only used in the first months of therapy or in specific situations) in other countries. Criteria for the reimbursement of PAP therapy also differ markedly between European countries and are likely to influence adherence and persistence. For example, while the fees paid to the home support providers in France increase as the number of hours of PAP use increases [30,31], in Belgium and Germany, nonadherence can result in the cessation of patient reimbursement.

The large number of patients treated with PAP therapy and the heterogeneity of home support provider service levels across Europe provide a unique opportunity to evaluate the optimal management approach. This requires an assessment of the added value of the service and of its impact on PAP adherence and persistence; quality of life; patient-reported outcomes (PROs), including quality of life and symptoms, patient-reported experience (PREs), and satisfaction.

Air Liquide Healthcare (ALH) is composed of several home support provider companies operating in more than 40 countries worldwide and 10 European countries. Support to patients with sleep apnea requiring PAP treatment is provided in all these countries. ALH designed the AWAIR (Assessment of the Benefit of the Home Support Provider Service Level Associated With Positive Airway Pressure Treatment in Patients With OSA on Treatment Adherence and Persistence: an International Real-World) study to assess and compare PAP adherence and persistence across 4 different European countries and according to the level of service. The study will consider the main confounding factors for adherence and persistence to PAP therapy and will provide unique information about differences in patient profiles across countries, PROs, OSA and PAP literacy, and experience and satisfaction with PAP therapy and service (PREs).

## Methods

### Study Design

This international, ambispective, real-world, cohort study is being conducted in 4 European countries (France, Belgium, Spain, and Portugal). It includes a retrospective analysis with the reuse of home support provider data routinely collected for PAP-related services and a prospective evaluation with the collection of patient data using a web-based patient questionnaire.

### Study Objectives

The main objective of the study is to compare PAP adherence and the PAP therapy persistence rate between countries and between different levels of home support provider service.

The study’s other objectives are to (1) identify service components that influence PAP adherence and persistence; (2) identify factors associated with PAP adherence and persistence; (3) describe in each country sociodemographic and OSA-related clinical characteristics, home support provider PAP-related service, OSA and PAP literacy of participants (perceived and actionable competence), patient experience and satisfaction with PAP therapy and home support provider support, patient-reported OSA symptoms, and quality of life (determined using the EQ-5D-5L questionnaire [32]); and (4) describe patterns of PAP use.

### Participants

#### Process for Selecting Patients

Eligible participants are adults (aged 18 years and older) who started PAP therapy between January 1, 2019, and December 31, 2023; for whom PAP services were delivered by an ALH affiliate in France, Belgium, Spain, or Portugal; and had a valid email address or smartphone number.

Potential participants were identified by applying these inclusion criteria to the data sourced from each home support provider database. In France and Portugal, all patients who met the above inclusion criteria were informed about the study. In Spain and Belgium, which have regional- or hospital-level regulatory processes, potential participants are only included from representative investigational sites. After providing the information about the study, patients who either consented to participate (Portugal, Spain, and Belgium) or did not “opt-out” (France) are enrolled in the study. These processes are described in more detail in the Ethical Considerations section.

The digital and decentralized nature of the study using e-consent and an electronic patient-reported outcome (ePRO) tool means that patients are not directly recruited by investigators. Instead, a secure electronic solution, [name], is used to provide direct and individual information about the study, obtain consent, and provide access to the web-based questionnaire. This solution is compliant with European and French legislation and regulations on the protection of personal data, as well as ethical guidance about patient’s rights management. Its technology is powered by blockchain thus guaranteeing full traceability on e-consents.

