### Ethical Considerations

The study protocol was developed in collaboration with a scientific committee composed of experts in OSA and methodologists from the 4 countries involved. The regulatory process and patient consent for a study with the reuse of data and a questionnaire were different for the 4 countries.

In France, the study followed the methodology MR-004 of the French Data Protection Authority (Commission Nationale Informatique et Liberté) concerning research that reuses data that have already been collected [33] and was approved by the local ethics committee of Angers University Hospital in November 2023 (2023-159). In Portugal, the study was considered observational and required approval by a central ethics committee; the approval was obtained from the ethics committee of Lisboa in May 2024 (24/24). In Spain, the study was considered observational and required approval by the ethics committee at each participating hospital; approval was obtained from the CEIm Hospital Universitario Ramón y Cajal of Madrid in July 2024 (095/24) and from the CEIm Hospital Universitario Doctor Peset of Valencia in December 2024 (127/24) and is pending for other regions. In Belgium, the study was considered interventional and required approval by a central ethics committee (Commissie voor Medische Ethiek Ziekenhuisnetwerk Antwerpen Institutional Review Board, Ziekenhuis aan de Stroom Middelheim) and by the local ethics committee at each participating hospital. Ethics approvals from the belgian central ethics committee are still pending.

In France, potential participants have the option to decline the reuse of their personal data through an “opt-out” process. Conversely, in Belgium, Portugal, and Spain, an “opt-in” process has been established, requiring explicit consent from participants to join the study.

No compensation is provided to participants.

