### Statistical Methods

#### Sample Size

This study aims to include all adults starting PAP therapy managed by an ALH home support provider in the participating countries who met the selection criteria during the study time period. This approach minimizes selection bias and sampling errors, ensuring precise and reliable results. Inclusions will be possible at the national level (France) or only at some investigational sites in countries requiring regional or hospital-level regulatory processes. All potential participants will be informed whenever ethics committee approval is obtained from the respective regions or hospitals. It is expected that around 30% of the 150,000 eligible participants will not be enrolled due to the absence of (or incorrect) email, or refusal to participate. Therefore, the number of included patients is expected to be around 100,000. With a sample of this size, the probability of showing a statistically significant difference in adherence between different levels of service if one exists is >99%, even if there were important imbalances between groups.

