### Strengths

One of the major strengths of this study is its large sample size, which enhances the representativeness of the population and the generalizability of the findings. The retrospective design allows for long-term evaluation of PAP adherence and persistence and ensures that there is no influence on participants’ behavior because data were collected prior to their inclusion in the study. In addition, the AWAIR study will describe between-country differences in home provider services and patient characteristics for the first time, and report on patient satisfaction and experience with PAP therapy.

In contrast with conventional clinical trials, the real-world setting ensures that the results will reflect the usual course of care [56]. This is particularly important for evaluating adherence because it minimizes the risk of bias that could arise from study participation. Furthermore, real-world evidence is particularly relevant for meeting health authority post-approval effectiveness requirements [57]. Well-conducted comparative effectiveness research can provide valid results similar to randomized trials for this measure of known confounding factors [56], and can use methods (such as stratification, matching, or regression analyses) to account for or adjust for such factors and yield valid results [58]. In the real-world comparative AWAIR study, adjustment for potential confounders identified through literature review and clinical expertise, combined with the use of hierarchical models accounting for contextual differences related to the international nature of the study, will help the data to provide an accurate assessment of the net effect of home provider services on PAP adherence and persistence while minimizing the potential biases inherent in real-world studies. Additionally, the use of an ePRO tool facilitates the collection of data on confounding factors that would not otherwise be available in the retrospective database analysis, along with PROs, PREs, and health literacy across a large and diverse patient population from various geographic regions [59].

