### Limitations

Selection bias cannot be entirely ruled out because participants were required to have a valid email address or smartphone number to be eligible for the study. This may lead to underrepresentation of certain subgroups of PAP users, such as older adults. Patients who answer the questionnaire might also differ from those who do not answer it. In addition, this study will only include individuals who use PAP supplied by a home support provider affiliated with ALH and it is possible that the level or content of additional services may differ slightly from other home support providers in the same country. To assess the potential impact of such biases, we will compare the characteristics of our study population with published data on OSA, focusing on age, sex, and disease severity.

Data from the ePRO tool may be subject to recall bias and inaccuracy because participants will complete the web-based questionnaire at variable periods of time since the start of PAP therapy (up to 5 years later for those who started PAP in 2019) and medical data will directly be provided by the patient. Confounding bias other than the key confounding factors considered is another limitation, particularly with respect to medical follow-up (data that will not be collected in this study).

Finally, the period over which this study was conducted included times before and during the COVID-19 pandemic (including lockdowns), and the worldwide recall of a PAP device made by Philips Respironics [36]. Sensitivity analyses will be performed to determine whether these factors had any influence on the overall study findings.

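### Opt-out enrolment in France and opt-in enrolment elsewhere expose the between-country comparison to selection on the outcome; the article says selection bias is minimized, and its planned check cannot detect this

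*Protocol article*

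**What the plan says.** Under Process for Selecting Patients, the enrolled are "patients who either consented to participate (Portugal, Spain, and Belgium) or did not" opt out (France). Ethical Considerations confirms both halves. "In France, potential participants have the option to decline the reuse of their personal data through an" opt-out process, whereas the other three countries use an opt-in process "requiring explicit consent from participants to join the study". Under Process for Contacting and Recruiting Patients, the invitation comes by email or SMS and leads to a login on a consent platform.

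Eligible patients "started PAP therapy between January 1, 2019, and December 31, 2023", and French enrolment opened in October 2024 (Results). The Strengths section notes that "data were collected prior to their inclusion in the study". Patient Datasets makes retrospective data available for included patients.

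The main objective is to "compare PAP adherence and the PAP therapy persistence rate between countries and between different levels of home support provider service". On selection, Sample Size says: "This approach minimizes selection bias and sampling errors, ensuring precise and reliable results". Limitations names three sources of selection: valid contact details, questionnaire response and the single provider group. It does not name the consent rule. Its check is that "we will compare the characteristics of our study population with published data on OSA, focusing on age, sex, and disease severity". The sensitivity analyses described concern COVID-19 lockdowns and the device recall.

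**The concern.** The consent rule coincides exactly with France versus the rest, and one main contrast is between countries. Because the outcome largely precedes consent, the decision to answer can depend on it. A patient who gave up PAP has less reason to answer a PAP provider's message and log in to a platform. In France that patient stays in the data by doing nothing; in the other three countries the patient disappears.

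If that happens, selection depends on the outcome in three countries and hardly at all in the fourth. The planned methods do not remove this from the country contrast:

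- Covariates adjust for patient differences, not for selection on the outcome itself.
- A country random effect models the shift but cannot tell it from a real country difference.
- The e-value is planned for unmeasured confounding, not for selection.
- A comparison of age, sex and severity with published OSA data can look entirely reassuring while adherence is heavily selected.

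At the planned size even a small shift would be statistically significant, and the results are meant to inform payers and authorities.

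**Working it through.** **The plan's own figures.** 150,000 × (1 − 0.30) = 105,000, against a stated figure of around 100,000. A loss of 33.3% gives exactly 100,000, so this is rounding. The stated power above 99% cannot be reproduced, because no significance level, effect size or group shares are given; nothing below depends on it.

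**What the totals imply about participation.** Results reports about 90,000 patients informed in France. Assume these are France's whole share of the 150,000, leaving 60,000 elsewhere, and assume 2% to 10% object in France.

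- 2% object: 88,200 French patients. Opt-in needed elsewhere is (100,000 − 88,200)/60,000 = 19.7%, or (105,000 − 88,200)/60,000 = 28%.
- 10% object: 81,000 French patients. Opt-in needed is 31.7% or 40%.
- If instead 10% were uncontactable in every country, French eligibles would be 100,000 and 45,000 others would be invited. With 2% objecting, opt-in needed is 11,800/45,000 = 26% to 16,800/45,000 = 37%.

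The stated totals are thus compatible with about 90-98% inclusion of informed French patients and about 20-40% of invitees elsewhere.

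**Size of the country bias.** Let p be true adherence (or persistence), equal in all countries, and RR = P(consent | adherent) / P(consent | non-adherent). Then

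- opt-in countries: observed = p·RR / (p·RR + 1 − p);
- France, assuming 3% of adherent and 3% × RR of non-adherent patients object: observed = 0.97p / [0.97p + (1 − p)(1 − 0.03·RR)].

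With p = 0.70 (assumed):

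| RR | Opt-in observed | Gap if France is unselected (70%) | Gap with French objection as above |
|---|---|---|---|
| 1.0 | 70.0% | 0 | 0 |
| 1.1 | 72.0% | 2.0 | 1.9 |
| 1.25 | 74.5% | 4.5 | 4.3 |
| 1.5 | 77.8% | 7.8 | 7.5 |
| 2 | 82.4% | 12.4 | 11.7 |
| 3 | 87.5% | 17.5 | 16.2 |

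At RR = 1.5 the last column becomes 8.9 points for p = 0.60 and 5.5 points for p = 0.80.

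**False significance.** Take 85,000 French and 15,000 other patients (assumed), France observed at 70%, no true difference and two-sided 5% testing. A ratio of 1.05 gives a significant result 71% of the time; a ratio of 1.10 gives one 99.8% of the time.

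**Service-level contrast.** One dataset was simulated per scenario with no true service effect, p = 0.70, RR = 1.5 (consent 37.5% versus 25%), 95% inclusion in France, and eligible numbers of 90,000, 20,000, 30,000 and 10,000 in France, Portugal, Spain and Belgium (the split is assumed). A linear mixed model with a random country intercept gave these service effects:

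- service level separates France from the other three: +7.2 points (SE 1.1);
- higher service covers all of Portugal and Spain and nowhere else: +3.9 points (SE 4.1);
- service varies within Portugal and Spain and consent does not depend on service: +0.4 points (SE 0.7).

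The random intercept absorbs a uniform shift where service varies within a country, and fails to where service and country coincide.

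**The case against.** **Selection on the outcome is not shown.** A reader might infer that the opt-in cohorts are demonstrably selected on adherence. The article gives no consent rate by PAP use, and equal consent would give no bias. This stands: the asymmetry is a fact, the bias an inference. Nor does the article describe how deaths are handled, so no claim about deceased patients can rest on it.

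**The service comparison need not inherit the bias.** The Abstract calls service levels country or area specific, and the Introduction places personalized plans in some regions of Spain and Portugal, so there may be within-country variation. This stands. The stronger reading, that every main contrast is biased in full, is not supported.

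**The adjusted models may already use completers.** Sleep duration, prior symptoms, education, occupation, bed sharing, comorbidities, smoking and alcohol come only from the questionnaire, so a fully adjusted complete-case model would be limited to those who answered it in all four countries. This is a fair point. But the article does not assign a population to the models, and Sample Size argues from about 100,000 included patients.

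**Completers as the main population would be a poor trade.** That would discard the least selected data in the study. It would also equalize the entry rule rather than the strength of selection, and completion may itself depend on experience of the service. This stands, and it makes the restriction a sensitivity analysis.

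**The consent rules follow national regulation, and an unseen analysis plan may hold weighting or selection analyses.** Both are true. The point therefore rests on what the article itself states: a claim the design does not support, a list of limitations without the consent rule, and a check that cannot detect this selection.

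**Conclusion.** The point holds for the between-country comparison. France includes silent invitees and the other three countries exclude them, largely after the outcome has occurred, so a difference in consent between PAP users and non-users passes in full into the country contrast. The statement that the approach minimizes selection bias is wrong for that contrast, and the published-data check cannot reveal the problem.

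The size is unknown. At 70% true adherence or persistence it runs from nil at a consent ratio of 1, through about 2 points at 1.1 and 7-8 at 1.5, to 16-18 at 3. These ratios, the French objection rate and the common true rate are all assumptions. For the service-level comparison the bias is conditional: near zero where service varies within countries and consent does not depend on service, and close to the full country bias where service level separates France from the rest.

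**What to change.** 1. **Wording.** In Sample Size, delete the selection-bias claim or limit it to sampling error. In Limitations, state that France enrols non-objectors and the other countries only active consenters, largely after the outcome, and that this limits the country comparison.
2. **Check.** Replace or supplement the published-data comparison with enrolment rates by country and a table of enrolled versus all eligible patients in each country. Use aggregate anonymous ERP counts by age band, sex, start year and still-in-therapy status, where regulation allows. Still-in-therapy status speaks to persistence directly and to hours of use only indirectly.
3. **Analysis.** Prespecify, as a sensitivity analysis and not as the main analysis, the comparison restricted to questionnaire completers in all four countries. Report service estimates within each country where service varies. Add a tipping-point analysis on the consent ratio. For a binary outcome with France treated as unselected, the ratio that would explain away an unadjusted difference is simply the observed odds ratio: for 77.8% versus 70%, 3.5/2.33 = 1.5. Readers can then judge whether that ratio is credible.

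Cost: some extra analysis, wider intervals in the restricted comparison, and possibly ethics or data-protection clearance for the aggregate counts. The list of eligible patients has already been extracted, and the consent procedures need not change.
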